### Study Visits

#### First Visit

During the first visit, the study’s purpose will be thoroughly explained to participants. Following this, informed consent will be obtained from parents or guardians, and assent will be sought from the child participants. No data will be collected if the participant withdraws consent from the study. The eligibility criteria (Table 1) will be reviewed to confirm participants’ suitability. Additionally, participants will be instructed to abstain from stimulant substances, such as caffeine, xanthines, or medications, 24-48 hours prior to the visit, depending on the type of treatment. If this time frame has not been adhered to, the study evaluation will be rescheduled for the following days.

**Table 1. T1:** Eligibility criteria for participants in the SINCRONIA study.

Participant group	Inclusion		Exclusion	
	Cases (ADHD^a^)	Pediatric controls (non-ADHD)	Cases (ADHD)	Pediatric controls (non-ADHD)
Agreement to participate, with written informed consent obtained from a legal representative together with their own assent	Yes	Yes	No	No
Age (years)	7-12	7-12	<7->13	<7->13
Right-handedness (recruitment of up to 10% of left-handed children is permitted)	Yes	Yes	No	No
Time schedule	ADHD diagnosis within the past 3 years or at the time of the study	Pediatric attendance within the past 3 years or at the time of the study	ADHD diagnosis more than 3 years before the time of the study	Pediatric attendance more than 3 years before the time of the study
Type of ADHD	Predominantly hyperactive/impulsive, or combined presentation, or predominantly inattentive presentation	—^b^	ADHD presentations different from those considered in the inclusion criteria	—
Neuropsychiatric comorbidities	Mild/moderate comorbid conditions (such as anxiety, dyslexia, or SCT^c^) that do not compromise participation	Mild/moderate comorbid conditions (such as anxiety, dyslexia, or SCT) that do not compromise participation	Severe comorbid conditions (such as autism or epilepsy) that may compromise participation	Severe comorbid conditions (such as autism or epilepsy) that may compromise participation
Color blindness or any other condition that may cause instrumental difficulties for sensorineural perception	No	No	Yes	Yes
Severe cognitive or behavioral problems or insufficient capacity to maintain a minimum level of relaxation and rest	No	No	Yes	Yes
Regular intake of medications other than the treatment of ADHD that may alter attentional or executive capacity	No	—	Yes	—

a ADHD: attention-deficit/hyperactivity disorder.

b Not applicable.

c SCT; sluggish cognitive tempo.

Sociodemographic and clinical data will be collected from eligible participants, including a physical assessment to document their maturation status (Tanner stage) and a record of all prior treatments at the time of this writing, including those for ADHD. Questionnaires will be administered to screen for relevant psychiatric disorders (SDQ) and comorbid conditions (CCI-2 and CABI). The WISC-V will be conducted as part of the neuropsychological evaluation. If the assessment is not completed during the first visit, an additional visit will be scheduled to complete the evaluation.

#### Second Visit

During the second visit, the suspension of medication and abstinence from stimulant substances such as caffeine and xanthines will be confirmed with the participants. Once both have been confirmed, the child’s head circumference will be measured to select the appropriate EEG cap size (S, M, or L). The cap will then be immersed in saline solution for 10 minutes before being placed on the child’s head. The impedance measured in ohms will be assessed at this point.

The EEG recording will begin with a trigger check and a 4-minute eyes-closed resting phase to record brain activity at baseline, followed by the task. The instructions for the task will be introduced, with example trials before full implementation of each part of the task. Throughout the task, breaks will be provided for brief play activities and impedance checks. The EEG session will conclude with the creation of a 3D model of cap placement while the child is wearing the cap.

#### Third Visit

During the third visit, the suspension of medication and abstinence from stimulant substances such as caffeine and xanthines will be again verified. Once both are confirmed, the neuropsychological evaluation will proceed with the administration of the CPT-3, the ENFEN, and additional tests to screen for comorbid conditions, such as PROLEXIA.

Although the sample size calculation indicates a total of 120 participants (40 per group), an additional 10 participants per group will be recruited to explore factors influencing diagnostic performance and SCT construct validity (Figure 1). Furthermore, an extra 10% will be added to account for nonassessable data, resulting in a total of 162 participants. This total may be slightly increased to ensure 54 participants per group after accounting for screening failures and protocol deviations. The maximum time interval between the index test and the reference standard is 72 hours; however, whenever feasible, a 24-hour interval will be pursued.

**Figure 1. F1:**
[figure not shown]
Procedure of the study. ADHD: attention deficit/hyperactivity disorder; CPT-3: Continuous Performance Test, Third Edition; EEG: Electroencephalogram; SDQ: Strengths and Difficulties Questionnaire.

### Planned Data Analysis

This clinical study focuses on the characterization and initial validation of an experimental medical diagnostic test under development. To avoid bias, the physicians involved in diagnosing and selecting the study groups will not participate in the analysis. Furthermore, missing data will not be imputed. In addition, indeterminate index test or reference standard results will not be allowed, as a positive or negative diagnosis will be required according to the previously defined cutoffs. Analyses will be performed on complete cases within each analysis set. The planned sample size (Multimedia Appendix 1) includes a margin for nonevaluable data (10% added for nonassessable data-complete-case analysis). No interim analyses or stopping rules are planned.

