## Methods

### Study Design

This is a noninterventional, case-control, cross-sectional, and assessor-blinded study, which is part of the development of a medical diagnostic test. This manuscript describes the latest version of the study protocol (HUPH-BP-BMCCEEG-CC22 version 4.0, approved on June 7, 2024, as Amendment 4), which was reviewed and approved by the appropriate ethics committee (see below). In order to allow for more complete and detailed reporting, we adhere to 2 acceptable reporting guidelines that match the study design: the Standards for Reporting Diagnostic Accuracy Studies (STARD; Checklist 2) and the SPIRIT (Standard Protocol Items: Recommendations for Interventional Trials) 2025 checklist (Checklist 1) of items to address in a randomized trial protocol, though, *sensu stricto*, our study is not a randomized trial. Following the terminology of the STARD, the EEG and the algorithms used to analyze the EEG data will be regarded as the index test, and the executive control task during which brain connectivity metrics will be pursued will be regarded as the index task. The best estimated diagnosis based on clinical interviews and neuropsychological assessment will be regarded as the reference test. To minimize bias, the PI establishing the reference standard will not perform EEG analyses or access EEG results. Blinding to index test results will be maintained, as no diagnostic or therapeutic decisions will be based on these findings. Consequently, no clinical decision will be influenced by information from the index test. Likewise, the team in charge of EEG processing will not have access to the clinical diagnosis data during data collection for the study. Participants will be categorized into 3 groups, including ADHD predominantly inattentive, ADHD combined or hyperactive/impulsive, and a control group, based on clinical evaluation including the reference CPT-3.

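### The complete-case rule limits the primary sensitivity and specificity to children with an assessable index test, and no analysis described in the article keeps the others in the denominator

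*Protocol article*

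**What the plan says.** Three rules appear together under Planned Data Analysis in the protocol article. First, "missing data will not be imputed". Second, "indeterminate index test or reference standard results will not be allowed, as a positive or negative diagnosis will be required", by reference to cutoffs set beforehand. Third, "Analyses will be performed on complete cases within each analysis set". The same paragraph ties the recruitment margin to the third rule: the planned sample size "includes a margin for nonevaluable data (10% added for nonassessable data-complete-case analysis".

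The section on the third visit gives the build-up: "the sample size calculation indicates a total of 120 participants (40 per group), an additional 10 participants per group will be recruited", and then "an extra 10% will be added to account for nonassessable data", for a total of 162, or 54 per group.

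The Hypotheses section sets the sensitivity reference at 0.90 with a noninferiority margin of −0.10, so the lower confidence limit must exceed 0.80. Under Diagnostic Performance of the Index Test, each component is judged by a 97.5% interval. Specificity must be superior to a threshold whose value is not in the article.

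On blinding, Study Design says that the EEG processing team "will not have access to the clinical diagnosis data during data collection for the study".

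**The concern.** In a diagnostic accuracy study, failure to obtain a readable index test is itself a result of using that test. Here the test is a 4-minute resting recording followed by three parts of 400 go/no-go trials, given to children aged 7 to 12, with cases off ADHD medication. Without imputation and with complete cases only, a child whose recording cannot be assessed drops out of both numerator and denominator. The primary sensitivity and specificity then answer a conditional question: how well does the test classify children from whom a usable recording was obtained?

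That question is legitimate, but it is narrower than the claim the article wants to support. The Statistical Analysis section speaks of a minimum performance threshold in the target population, and the Participants section defines that population as symptomatic children who contact the health system. If failures are not rare, the sensitivity criterion can be met on complete cases and missed once failures are counted. The article describes no analysis that would show this.

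**Working it through.** **Step 1. The plan's own margin.** Inputs from the third-visit section: 40 per group by calculation, 10 more per group for exploratory aims, and 10% for nonassessable data. Taking the 10% on the calculated 40 gives 3 × (40 + 10 + 4) = 162, which matches the stated total. The margin is thus 4 of 54 per group, or 4/54 = 7.4%. It covers nonassessable data in general and is not stated to be an EEG failure rate.

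**Step 2. Formula.** Let Se be sensitivity among assessable cases and f the share of cases that are unassessable. If failures count as missed, sensitivity over all cases is Se × (1 − f).

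**Step 3. Illustration for sensitivity.** Assumptions:
- 108 ADHD cases (two groups of 54).
- The whole margin is used up by unassessable index tests, so 8 of 108.
- 90% of the remaining 100 are detected.

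Clopper-Pearson 97.5% intervals against the 0.80 bound:
- Complete cases: 90/100 = 0.900, interval 0.812 to 0.956. Clears 0.80.
- Failures counted as missed: 90/108 = 0.833, interval 0.737 to 0.906. Does not clear 0.80.

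**Step 4. Other assumptions.** Values of Se × (1 − f):

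| Se among assessable | f = 2% | f = 5% | f = 10% |
|---|---|---|---|
| 0.90 | 0.882 | 0.855 | 0.810 |
| 0.95 | 0.931 | 0.902 | 0.855 |

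- With 95% detected and 5% unusable, sensitivity is 0.95 × 0.95 = 0.9025. With 108 cases the lower limit is about 0.82, so the criterion is still met.
- With 95% detected and 8 of 108 unusable, sensitivity is 95/108 = 0.880 with lower limit 0.791, so it is not met.
- The 90/100 example lies on the edge of the pass region: 89/100 has a lower limit just under 0.80 (0.7999).

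**Step 5. Both measures, under different rules for failures.** Assume also 54 controls, 4 of them unassessable, and 45 of the other 50 correctly negative.

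| Rule for failures | Sensitivity | Specificity |
|---|---|---|
| Complete cases | 90/100 = 0.900 | 45/50 = 0.900 |
| All positive | 98/108 = 0.907 | 45/54 = 0.833 |
| All negative | 90/108 = 0.833 | 49/54 = 0.907 |
| Misclassified in both groups | 90/108 = 0.833 | 45/54 = 0.833 |

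Under either consistent rule (all positive or all negative) one measure falls and the other rises slightly. Both fall only under the last rule, which depends on the true diagnosis and is therefore a worst-case bound. A pass or fail for specificity cannot be worked out, because its threshold is not in the article.

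**The case against.** The best defence is that this is an initial validation of a test under development, for which accuracy among valid recordings is a sensible first target. The article discloses part of the restriction. Table 1 excludes children who cannot stay minimally relaxed and at rest, and Strengths and Limitations describes the sample as children able to tolerate the EEG sessions. Definitions of analysis sets, failure counts and supplementary analyses may sit in the full protocol or the analysis plan. All of this stands as an argument for keeping the complete-case analysis as primary. It does not remove the point, because the article itself fixes the rule that decides who is counted.

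A reader might go further in four ways that the text does not support.

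- **That indeterminate results are thrown away.** The clause requires a positive or negative call at the cutoff, so borderline children stay in the table. It simply cannot classify a recording that is not there.
- **That the plan expects 10% of EEGs to fail.** The margin is for nonassessable data generally and could equally cover incomplete reference data.
- **That sensitivity and specificity are both overstated.** This holds only under the worst-case rule in Step 5.
- **That assessability will be judged with diagnoses known, or that failures are commoner in hyperactive children.** The blinding of the processing team is stated only for the data collection period, and training a classifier needs labels afterwards. The article does not say when assessability is decided. A link between failure and hyperactivity is plausible, but no figure in the article supports it.

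**Conclusion.** The point holds in limited form. By the article's own rules, the primary sensitivity and specificity are conditional on an assessable index test, and the article describes no companion analysis that counts the children who fail it. How much this matters depends on a failure rate that is not given. If the plan's margin of 4 per group were all unassessable index tests and 90% of the remaining cases were detected, counting failures as missed would lower sensitivity by 0.900 − 0.833 = 0.067 and reverse the conclusion at 0.80. With higher detection and fewer failures the conclusion survives. The group sizes, the attribution of the margin to the index test and the detection rates are assumptions. This is worth correcting before the results are analysed, but it does not invalidate the primary analysis.

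**What to change.** - Keep the complete-case analysis as primary.
- Report the number and share of unassessable EEGs in each of the three groups.
- Add a supplementary intention-to-diagnose analysis that keeps every child with a reference diagnosis. Show failures as all positive, as all negative, and as misclassified in both groups, with the last labelled a worst-case bound.
- State that assessability of each recording is decided and locked before diagnoses are linked to the EEG data.
- Limit the claim of acceptable performance to children with an assessable recording, unless the intention-to-diagnose result also meets the criteria.

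No new data are needed, so the end of recruitment is no obstacle. The cost is one extra table and a documented lock step; the downside is that the figures may be less favourable.

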#### Hypotheses

The primary hypothesis, though involving 3 participant groups, focuses on demonstrating a minimum diagnostic performance to distinguish between the ADHD group as a whole and the pediatric control group. Regarding the true positive fraction (true positive fraction [TPF] or sensitivity), due to its high acceptability threshold (TPF_0_=0.90), a noninferiority test will be used for this dimension, with a noninferiority margin of δT_0_=−0.10. Since the primary objective is to determine whether the index test yields classification probabilities—TPF and false positive fraction (false positive fraction [FPF] or 1-specificity)—that are minimally acceptable (TPF_0_ and FPF_0_), the corresponding hypothesis, considering the noninferiority assumption for sensitivity, can be formally stated as:

(1)$$H_{0}:\left\{TPF-TPF_{0}\leq \delta \;\overset{T}{\underset{0}{\cup }}FPF\geq FPF_{0}\right\}$$

If H_0_ can be rejected, TPF−TPF_0_ > δ$\begin{array}{c} T\\ 0 \end{array}$ and FPF<FPF_0_; therefore, the index test would be noninferior to a hypothetical test with 90% sensitivity and superior to a hypothetical test with a specificity of 1−FPF_0_.

Two additional pairwise comparisons will be conducted: one between each ADHD group and pediatric controls, and another between the ADHD groups themselves, with hypotheses formulated as previously described. The Hochberg procedure will be used to control Type I error [70].

Biomarker identification will use dimensionality reduction methods, which are descriptive and do not require hypothesis testing or multiplicity adjustments.

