#### Statistical Analysis

The primary objective will be to assess the diagnostic accuracy of the index test in terms of classification probabilities, specifically sensitivity and specificity. Sample size calculation ensures a minimum performance threshold within the target population.

This objective is interdependent with another primary aim, identifying the minimal set of biomarkers that optimize the diagnostic performance of the index test. As this objective does not involve hypothesis testing, adjustments for multiplicity are unnecessary.

The analyses of the secondary objectives will be exploratory, except for the first, which shares the hypothesis-free nature of biomarker identification. Tertiary objectives will also be exploratory, focusing on the validity of the SCT construct and EEG signal preprocessing systems. These analyses may be expanded in future studies to identify EEG-based clusters associated with ADHD symptomatology.

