#### Analysis of Primary Parameters

The analysis of diagnostic accuracy requires preliminary analyses to identify biomarkers that optimize the diagnostic performance and to develop a classification algorithm based on biomarker values across the three study groups defined by the clinical team, serving as the reference test. The first secondary parameter, essential for evaluating the primary parameter, will also be analyzed in a confirmatory fashion without explicit hypothesis testing.

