#### Diagnostic Performance of the Index Test

The primary parameters are the classification probabilities of the index test relative to the reference test. In addition to these classification probabilities, positive and negative predictive values (PPV and NPV, respectively) and diagnostic likelihood ratios will be calculated. Inferences will be made by calculating 95% asymmetric rectangular confidence regions for each pair of interest values (TPF and FPF), (PPV and NPV), and (DLR^+^ and DLR^−^). Confidence regions will be calculated from the cross-product of the 97.5% confidence intervals of each component in each pair. Sensitivity values will be assessed for noninferiority (and potentially superiority), while specificity will be evaluated for strict superiority. In addition to naive predictive value estimates, which will be biased by design, other estimates will be adjusted using external prevalence data and diagnostic likelihood ratios or Bayesian multiplication factors to mediate prior and posterior probabilities:

, (2)$$logit\;PPV=logit\;\rho +\log{DLR}^{+}$$

, (3)$$logit\;NPV=-logit\;\rho \;+\;-\log{DLR}^{-}$$

where ρ is the prevalence in the target population (7.0% [71]). Clinical information and reference standard results will not be available to the performers of the index test. Furthermore, the reference standard will be performed after the index test. Moreover, performers of the index test will neither be involved in the technological processing nor the statistical analyses of either the index or the reference standard tests. Finally, cross-tabulation of the index test results (or their distribution) by the results of the reference standard will be considered.

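### The Hochberg family is announced as two pairwise comparisons but three are described, and fixed 97.5% intervals alone cannot carry out the step-up rule

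*Protocol article*

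**What the plan says.** All references are to the protocol article.

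- **Hypotheses.** The primary null (equation 1) is a union: sensitivity (TPF) is too low, or the false positive fraction (FPF) is too high. It is rejected only if both parts are rejected. The section then adds: "Two additional pairwise comparisons will be conducted: one between each ADHD group and pediatric controls, and another between the ADHD groups themselves". These have formal nulls of the same kind ("with hypotheses formulated as previously described"), and "The Hochberg procedure will be used to control Type I error". The members of the family and the value of alpha are not given.
- **Diagnostic Performance of the Index Test.** "Inferences will be made by calculating 95% asymmetric rectangular confidence regions for each pair of interest values". "Confidence regions will be calculated from the cross-product of the 97.5% confidence intervals of each component in each pair". Both component tests are directional: "Sensitivity values will be assessed for noninferiority (and potentially superiority), while specificity will be evaluated for strict superiority". Whether the 97.5% intervals are one-sided or two-sided is not stated.

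**The concern.** Hochberg compares the ordered p-values with alpha, alpha/2, and so on down to alpha/m, so m has to be right. An analyst who takes the announced count at face value would stop at alpha/2, or would leave one of the three contrasts outside the family. Either way the error rate across the subtype contrasts would exceed the nominal level.

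Two further matters follow from the choice of rectangles as the basis of inference. A region at one fixed level does not supply the several levels that a step-up rule needs. And splitting the error between the two components is what joint estimation requires, whereas a union null that falls only when both halves succeed does not require it. The subtype claims could therefore be under-protected while the primary test gives up power without need.

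**Working it through.** **1. The plan's own joint level.** Two 97.5% intervals give 0.975 × 0.975 = 0.9506 if independent, and at least 1 − 2 × 0.025 = 0.95 by Bonferroni. The stated 95% region is reproduced.

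**2. Count.** Inattentive versus controls, combined or hyperactive/impulsive versus controls, and one ADHD group versus the other: 2 + 1 = 3, which is every pair of three groups.

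**3. Hochberg thresholds.** Alpha is not stated, so two values are shown.

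| m | alpha = 2.5% | alpha = 5% |
|---|---|---|
| 2 | 2.5%, 1.25% | 5%, 2.5% |
| 3 | 2.5%, 1.25%, 0.83% | 5%, 2.5%, 1.67% |
| 4 (primary included) | adds 0.625% | adds 1.25% |

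**4. Familywise error with three independent true nulls and uniform p-values.**

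- m = 3 applied correctly: by simulation, just under 2.5% and just under 5%.
- Stepping stops at alpha/2. Something is rejected if the smallest p is at most alpha/2 or the largest is at most alpha, so the error is 1 − (1 − alpha/2)³ + (alpha/2)³.
  - alpha = 2.5%: 1 − 0.9875³ + 0.0125³ = 0.0370.
  - alpha = 5%: 1 − 0.975³ + 0.025³ = 0.0732.
- Third contrast tested at alpha outside a family of two: 1 − 0.975² = 4.9%, and 1 − 0.95² = 9.75%.

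**5. What a fixed rectangle can show.** A 97.5% interval shows only whether its one-sided p-value is at most 1.25% (two-sided interval) or at most 2.5% (one-sided bound). That is one level, not three. Three independent comparisons each judged at that level give 1 − 0.9875³ = 3.7% or 1 − 0.975³ = 7.3%.

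**6. The primary union null.** If the null is true, at least one half is true, and the chance of rejecting both halves cannot exceed the chance of rejecting the true one. The maximum Type I error is therefore the level of a single component. With 97.5% intervals it is 1.25% if they are two-sided and 2.5% if they are one-sided bounds.

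**7. Power of the sensitivity half.** The null boundary is 0.90 − 0.10 = 0.80 (Hypotheses). The number of cases is 2 × (40 + 10) = 100 (Third Visit). The true sensitivity is an assumption. With the Wilson (score) criterion, the standard error under the null is √(0.80 × 0.20/100) = 0.04.

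- One-sided 1.25%: 0.80 + 2.241 × 0.04 = 0.8897, so at least 89 of 100 must be correct.
- One-sided 2.5%: 0.80 + 1.960 × 0.04 = 0.8784, so at least 88 of 100.

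| Cases | Assumed true TPF | Power at 1.25% | Power at 2.5% |
|---|---|---|---|
| 100 | 0.90 | 70% | 80% |
| 100 | 0.95 | 99.6% | 99.9% |
| 110 (two thirds of 165) | 0.90 | 69% | 79% |
| 80 (base calculation) | 0.90 | 45% | 59% |

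**The case against.** The announced number may mean two kinds of comparison, and the article nowhere says that Hochberg will be run with m = 2. That is fair. The inflation is what would follow from taking the stated count literally, not a result that the plan commits to. The figures also lie at the upper end. The contrasts share participants, so they are not independent. Each null is itself a union, so the larger of its two p-values is close to uniform only when the other half is almost certain to succeed. None of this supplies m, and the sentence as written still does not add up.

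The rectangles do not exclude separate p-values, which the full protocol or analysis plan may define. This also stands. What remains is narrower: the rectangles, the only basis of inference that the article describes, do not implement the procedure that it names.

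On the primary test, sidedness is not stated, and the split never inflates error. The rectangle is a proper joint estimation region and is used in the same way for predictive values and likelihood ratios. If the components are one-sided bounds, each half already runs at 2.5% and nothing is lost at that level.

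A reader might also infer that the article contradicts itself on the status of the subtype tests, because it says elsewhere: "The analyses of the secondary objectives will be exploratory, except for the first, which shares the hypothesis-free nature of biomarker identification", and of the first secondary parameter that it "will also be analyzed in a confirmatory fashion without explicit hypothesis testing". The documents do not support this. Those sentences concern the first secondary objective, which is to develop and optimise the classification algorithm. The pairwise tests are presented separately, as additions to the primary hypothesis. The two conflict only if they are equated, and the article does not equate them.

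**Conclusion.** The count is wrong on a plain reading: three comparisons are described and two are announced. A family of two would not control error across them. The excess is about 3.7% against 2.5%, or 7.3% against 5%, assuming three independent true nulls with uniform p-values and stepping that stops at alpha/2. This illustrates the worst case and does not predict the trial's error rate. Fixed 97.5% intervals alone cannot carry out the Hochberg steps.

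For the primary hypothesis, the structural point holds: a union null needs no split. Its practical size is conditional. It is about 10 percentage points of power for the sensitivity half if the intervals are two-sided and the true sensitivity is 0.90, negligible at 0.95, and nil at the 2.5% level if the intervals are one-sided bounds. It would be wrong to conclude that the primary test is invalid or certainly underpowered on this account.

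**What to change.** Change the analysis wording before the diagnostic results are analysed:

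1. In Hypotheses, write three pairwise comparisons and list them.
2. Apply Hochberg with m = 3, or with m = 4 if the primary hypothesis belongs to the family, and say which. State alpha.
3. Give each comparison one p-value: the larger of its two one-sided p-values (sensitivity and FPF).
4. For the primary null, state that it is an intersection-union test with each half at the full one-sided level, and keep the 97.5% rectangle for joint estimation. State whether the intervals are one-sided or two-sided. If they are two-sided, this raises each half from one-sided 1.25% to 2.5%.

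Testing the subtype contrasts only after the primary null is rejected is an option, not a correction.

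The cost is wording only, with no new data or participants. The downside is a stricter smallest threshold for subtype claims: alpha/3 instead of alpha/2, that is 0.83% instead of 1.25% at alpha = 2.5%, or 1.67% instead of 2.5% at alpha = 5%. With m = 4 it is stricter still.
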